#### Secondary outcomes

Secondary outcomes will be measured in blood, urine, and stool samples. The metric used will be changes in means from the beginning to the end of each dietary intervention. Stool samples will be analyzed to assess:
Changes from baseline in the composition of the GM, assessed by 16S rRNA gene-based next-generation sequencing on the Illumina MiSeq platform. Total microbial DNA will be extracted from feces using the repeated bead-beating plus column method, as previously described [18]. The V3 and V4 hypervariable regions of the 16S rRNA gene will be sequenced following the Illumina protocol for 16S Metagenomic Sequencing Library Preparation.Change from baseline in fecal SCFAs assessed by gas chromatography - mass spectrometry (GC-MS). The metabolomic analysis of fecal waters will be performed after sample preparation involving solid phase microextraction (SPME), followed by GC-MS analysis to detect the volatile metabolites [4].Change from baseline in the fecal inflammatory profile assessed by the cytofluorimetric approach. In particular, superficial (CD3, CD4, CD8) and intracytoplasmic (transforming growth factor (TGF)-ß, interferon gamma (IFN)-γ, interleukin (IL)-4, IL-9, IL-10, IL-17, IL-10, IL-22, FoxP3) cell markers will be analyzed. The cells will be analyzed by the BD FACScan Cytofluorimeter using the Diva software (BD Biosciences, San Jose, USA). The concentration of cytokines, chemokines, and growth factors, including interleukins, IFN-γ, tumor necrosis factor (TNF)-α, growth-regulated oncogene-α (Gro-α), monocyte chemoattractant protein-1 (MCP-1), macrophage inflammatory protein-1ß (MIP-1ß), granulocyte colony-stimulating factor (G-CSF), and granulocyte-macrophage colony-stimulating factor (GM-CSF) will be determined in the fecal solutions according to the methodology of Munoz-González et al. [19].

Blood samples will be analyzed to assess:
Change from baseline in the inflammatory profile assessed by the cytofluorimetric approach. It will be assessed using the Bio-Plex cytokine assay (Bio-Rad Laboratories Inc., Hercules, CA, USA), according to the manufacturer’s instructions. In particular, IL-1ra, IL-4, IL-6, IL-8, IL-10, IL-12, IL-17, MCP-1, MIP-1ß, vascular endothelial growth factor (VEGF), TNF-α, IFN-γ, and IFN-γ-induced protein (IP)-10 will be measured.Change from baseline in the lipid peroxidation markers assessed by spectrophotometry. It will be estimated using the thiobarbituric acid reactive substances (TBARS) assay kit [20].Change from baseline in plasma total antioxidant capacity (TAC) assessed by fluorometry, using oxygen radical absorbance capacity [21].Change from baseline in reactive oxygen species (ROS) assessed by flow cytometry. In particular, leukocyte subpopulations (lymphocyte, monocyte, and granulocyte) ROS will be measured [22].

Urine samples will be analyzed to assess:
*1,4-dihydroxynonane mercapturic acid (DHN-MA) change from baseline*, assessed by enzyme immunoassay using polyclonal antibodies [23]. This specific biomarker is the major urinary metabolite of 4- hydroxy-2-nonenal, a lipid peroxidation product.

### Sample size calculation

Due to the lack of dietary intervention trials on BS and to the fact that gastrointestinal symptoms are quite similar in BS and inflammatory bowel disease, based on a previously published trial [24], a sample size of 80 individuals with BS is required to achieve power of 80% (beta) with alpha = 0.05, to detect a 50-point difference in the mean of SSS (the primary outcome), between VD and MD interventions. We will recruit an extra 10 volunteers (for a total of 90), as we assume that not all individuals would be compliant with the treatments and in case of loss to follow up. Losses will be included in the intention-to-treat but not in the per-protocol analyses.

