**Methods:**

This is a randomized, open, cross-over study that involves 90 individuals with BS, who will be randomly assigned to one of three different diets for 3 months: a lacto-ovo-vegetarian diet (VD), a Mediterranean diet (MD), or a Mediterranean diet supplemented with butyrate (MD-Bt). The VD will contain inulin-resistant and resistant-starch-rich foods, eggs, and dairy in addition to plant-based food, but it will not contain meat, poultry, or fish. The MD will contain all food categories and will provide two portions per week of fish and three portions per week of fresh and processed meat. The MD-Bt will be similar to the MD but supplemented with 1.8 g/day of oral butyrate. The three different diets will be isocaloric and related to the participants’ nutritional requirements. Anthropometric measurements, body composition, blood, and fecal samples will be obtained from each participant at the beginning and the end of each intervention phase. The primary outcomes will be represented by the change from baseline of the BS gastrointestinal and systemic symptoms. Changes from baseline in GM composition, short-chain fatty acid (SCFA) production, and the inflammatory and antioxidant profile will be considered as secondary outcomes.

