### Outcome measures

#### Primary outcomes

Primary outcomes will be assessed through validated questionnaires, to analyze the progression of BS. The metric used will be changes in means from the beginning to the end of each dietary intervention. They will include:
Severity of gastrointestinal symptoms assessed by the SSS modified form. The SSS is a multidimensional rating scale assessing overall symptom severity on a visual analogue scale (VAS). An overall score will be calculated from six items: pain severity, pain frequency, abdominal bloating, dissatisfactory bowel habit, abdominal heaviness, and life interference. The modified SSS ranges from 0 to 600, with higher scores meaning more severe symptoms.Improvement of gastrointestinal-related BS symptoms assessed by the GAI modified form. The GAI will assess improvement of symptoms of BS using a 7-point scale, with higher scores meaning an improvement in the symptoms. The severity of abdominal pain, severity of abdominal distention, satisfaction with bowel habits, severity of headache, severity of exhaustion, severity of nausea, attention disorder, muscle/joint pain, and quality of life will be investigated in response to the following question: “Compared to the way you felt before you entered the study, have your symptoms over the past 7 days been: 1) “Substantially Worse”, 2)” Moderately Worse, 3)” Slightly Worse”, 4)” No Change”, 5)” Slightly Improved”, 6)” Moderately Improved” or 7) “Substantially Improved”.Disease severity in BS assessed by the BDCAF. The BDCAF will assess the presence of oral and genital ulceration, skin, joint, and gastrointestinal involvement, presence of fatigue and headache, using a 5-point scale according to the duration of symptoms, with 0 meaning no symptoms and 4 meaning symptoms for 4 weeks. The presence of eye, large vessel, or central nervous system (CNS) involvement will be documented with “yes/no” answers. In addition, individuals will be asked to rate on a 7-point scale how active they felt. Similarly, clinicians will complete a 7-point rating scale to assess their opinion of overall disease activity, with lower scores representing better outcomes.

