Before starting the data analysis, the level, pattern and likely causes of the missingness in the baseline variables and outcomes will be investigated by preparing appropriate tables. This information will be used to determine whether the level and type of missing data has the potential to introduce bias into the analysis results or substantially reduce the precision of estimates for the proposed statistical methods. Sensitivity analyses will be undertaken, based on the assumption that missing outcomes are the worst possible, or the best possible, in different randomization groups. If these show that conclusions may differ based on missing values, then supplementary multiple imputations for missing values will be undertaken. These analyses will account for results of any losses to follow up insofar as they pertain to differences in measured variables (i.e. under the assumption of missing at random). Finally, subgroup analyses will be performed to analyze possible differences in the changes according to some characteristics of the study population, such as age, sex, categories of BMI, and physical activity. A *p* value <0.05 will be considered statistically significant. Statistical analyses will be performed using SPSS software for Macintosh (SPSS Inc., Chicago, IL, USA).

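### The protocol article contradicts itself on what is primary: it sizes one comparison (SSS, VD vs MD) but declares three primary outcomes, so alpha 0.05 and 80% power cover only one of the declared tests

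*Protocol article*

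**What the plan says.** All references are to the protocol article.

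- **Sample size calculation.** Eighty participants are "required to achieve power of 80% (beta) with alpha = 0.05", and the target is "to detect a 50-point difference in the mean of SSS (the primary outcome), between VD and MD interventions". SSS is the primary outcome, in the singular, and one of the diet contrasts is sized. Ten more participants are added for non-compliance and loss to follow-up.
- **Primary outcomes.** The section opens in the plural: "Primary outcomes will be assessed through validated questionnaires, to analyze the progression of BS". It then lists SSS (one overall score, 0 to 600), GAI and BDCAF, with no ranking.
- **Abstract, Methods.** Also plural, and wider than the gut: "The primary outcomes will be represented by the change from baseline of the BS gastrointestinal and systemic symptoms".
- **Introduction (aim) and Study design.** VD and MD-Bt are both of interest, and MD is the control.
- **Statistical analysis.** A p "value <0.05 will be considered statistically significant". A Benjamini-Hochberg correction is stated at the end of the paragraph on sequencing, diversity and taxon tests. Nothing links it to the clinical outcomes.

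**The concern.** The sample-size section and the outcome section cannot both define the confirmatory test. Under the first, the trial succeeds or fails on SSS for VD vs MD, and alpha 0.05 and 80% power describe that test. Under the second, GAI and BDCAF have equal standing, and the aim brings in MD-Bt vs MD as well. The article does not say whether one success suffices or all are needed, and it gives no order or division of alpha.

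A significant result on any one scale, for either diet, could then be reported as meeting a primary outcome, and readers could not tell whether the sized hypothesis had succeeded. This matters more because participants know their diet and the outcomes rest largely on their own symptom ratings.

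**Working it through.** **1. The plan's own figure.** Inputs from Sample size calculation: difference 50 points, power 80%, alpha 0.05 (sidedness not stated; two-sided assumed), N = 80. The article gives no SD or within-person correlation, so N = 80 cannot be reproduced. It can only be solved backwards, with z(0.975) + z(0.80) = 1.960 + 0.842 = 2.802:

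- all 80 paired: SD of differences = 50 × √80 / 2.802 ≈ 159.6
- two independent groups of 40: SD = 50 / (2.802 × √(2/40)) ≈ 79.8

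Neither value can be checked against the article. The steps below need only the stated power and alpha.

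**2. Tests that could carry a primary claim.** Three scales are declared primary. The contrast family is not fixed, so each reading is shown:

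- VD vs MD only: 3 × 1 = 3 tests
- VD and MD-Bt each against MD: 3 × 2 = 6 tests
- all three diet pairs: 3 × 3 = 9 tests

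**3. Familywise error if any one success counts.** For fully independent tests it is 1 − 0.95^m: 14.3% for m = 3, 26.5% for m = 6 and 37.0% for m = 9. Contrasts that share a diet are correlated, which lowers the 6- and 9-test figures. A simulation of 1,000,000 draws used normal test statistics, a common correlation ρ between the three scales, diet means of equal variance shared across contrasts, and each test at its nominal two-sided 5%. The article gives no ρ, so a range is assumed.

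| ρ | VD vs MD only | Two contrasts vs MD | All three pairs |
|---|---|---|---|
| 0 | 14.2% | 24.7% | 32.3% |
| 0.5 | 12.6% | 21.9% | 28.5% |
| 0.7 | 10.9% | 19.2% | 24.9% |
| 0.9 | 8.3% | 14.9% | 19.5% |

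For comparison, SSS alone over all three pairs gives 12.2%, and SSS for VD vs MD alone gives 5%.

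**4. What error control would cost in power.** Keep N = 80 and the effect behind the stated 80%. Power at level 0.05/m is Φ(2.802 − z(1 − 0.05/(2m))), and the N that restores 80% is 80 × [(z(1 − 0.05/(2m)) + 0.842)/2.802]².

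| m | Power at N = 80 | N for 80% |
|---|---|---|
| 3 | 66% | 107 |
| 6 | 56% | 124 |
| 9 | 51% | 134 |

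These are Bonferroni figures. Holm's procedure gives at least this power for a given test and at most 80%. In a fixed order, the first test keeps the full 0.05 and the stated 80%.

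**The case against.** The strongest reply is that only a condensed article is at hand. Testing order, division of alpha and the scoring of GAI and BDCAF commonly sit in the full protocol or statistical analysis plan, so their absence here is not a defect. That stands, and the point does not rest on it. It rests on two statements in the article that disagree; a plan can settle them only by overriding one.

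Three stronger readings are tempting, and the article does not support them.

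- **That the chance of a false primary claim is 25–32%.** This needs all three diet pairs, an outcome correlation of at most 0.7 and a rule that any one success counts. The article states none of these. With MD named as control, two contrasts are the more natural family, and their range lies at or below 25%. The scales share gastrointestinal content, so positive correlation is likely and the uncorrelated figure is the least plausible.
- **That every GAI and BDCAF item would be tested, giving dozens of primary tests.** No section plans item-by-item testing. Naming no summary score is not a plan to test each item, and SSS has one stated total.
- **That the article has no error control at all.** It has a false-discovery correction, placed with the microbiota analyses. The gap concerns the clinical primary outcomes.

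In the other direction, Statistical analysis also plans within-diet paired tests. Counting those nine would raise the all-pairs figure to about 29–46%, but the article does not say that they carry the primary claim.

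It is also fair to say that demoting GAI and BDCAF is one solution among several. It takes systemic disease activity out of the primary objective, although the abstract places it there.

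**Conclusion.** The concern holds as an internal contradiction. Sample size calculation has one primary outcome and one sized contrast; Primary outcomes and the abstract have several; the aim adds MD-Bt against MD. With a general p<0.05 and no correction tied to the clinical outcomes, alpha 0.05 and 80% power are secured for only one of the declared primary tests.

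The size depends on how the contradiction is resolved. It is 5% if SSS for VD vs MD is the sole primary test. If any one of the three scales suffices, it is about 15–25% for the two contrasts against MD and 19.5–32% for all three pairs. These ranges assume correlations of 0.9 down to 0 and tests that hold their nominal level. They are illustrations under stated assumptions, since the article fixes neither the family nor the correlation.

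**What to change.** 1. State SSS, VD vs MD, at two-sided 0.05 as the single confirmatory comparison, as already sized.
2. If it is significant, test SSS for MD-Bt vs MD at 0.05 as the next step in a fixed order.
3. Make GAI and BDCAF secondary, with one named summary measure each. Place them later in the order, or report estimates with confidence intervals and no confirmatory claim.
4. Bring the abstract, Primary outcomes and Sample size calculation into agreement. Make the change before any outcome data are seen by diet.

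The cost is text, plus the co-primary status of GAI and of BDCAF, which carries systemic disease activity. Sample size is unchanged and the sized comparison loses no power. The article gives no power for MD-Bt vs MD, so none should be claimed for that step without its own assumptions.

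If the sponsor prefers to keep all three scales primary, apply a familywise procedure such as Holm over a stated family and restate the power. At N = 80 the guaranteed power for the sized test is then 66%, 56% or 51% for families of 3, 6 or 9 tests.

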### Recruitment and randomization

Participants will be recruited from the Behçet Center and Lupus Clinic, Careggi University Hospital, Florence, Italy, or using advertisements on local media, newspapers, social media and websites. After approval and completion of the initial assessment, the participants will be formally included in the study and randomized 1:1:1 to the three intervention arms through a web-based online randomization procedure. No adaptive randomization procedures will be performed. The random allocation sequence will be produced and managed by an independent staff member who is outside of the project, to code the treatments, and maintain the key to this code until data collection is completed.

### Blinding

Although full blinding of both participants and dieticians to treatments in this study is not possible because of obvious differences between the intervention diets, several strategies will be employed to reduce the risk of bias. First of all, the treatment allocation for each individual will not be revealed until the individual has irrevocably been entered into the trial, to avoid selection bias. In addition, outcome measures in the present study cannot be easily influenced by the observer. Furthermore, trial personnel who will enroll participants, data collectors, outcome assessors, and data analysts will be blinded to treatment allocation, and an employee outside of the research team will insert data into the computer in separate datasheets. On the other hand, making the trial open rather than blinded may improve recruitment. Unblinding will be permissible only when knowledge of the treatment will be absolutely essential for further management of the individual.

### Data collection

Follow-up assessments and data collection will be undertaken at the Unit of Clinical Nutrition of the Careggi University Hospital, Florence, Italy, by trial personnel. All participants will be examined between 7.30 and 11.30 a.m. after a 12 h-fasting period.

#### Compliance

Compliance with the interventions will be achieved using behavior change strategies including self-monitoring, and regular phone calls for dietary counseling. In particular, participants will receive at least one unannounced phone call during each intervention, in which participants will recall his or her 24-h diet period. Furthermore, participants will be provided with a detailed one-week menu plan for each dietary period with all foods expressed in weight and/or volume measures, and a hand-out containing details on their assigned diet, including food groups that can be included and ones that should be avoided. The vegetarian menu plan will also include recipes for preparing meals. Participants may discontinue the intervention or withdraw from the study for the following reasons: (1) at the request of the participant; (2) if the investigator considers that a participant’s health will be compromised due to adverse events or concomitant illness that develop after entering the study. Participants prematurely discontinued from the study before the 3-month evaluation will have the baseline clinical and laboratory evaluations performed.

#### Anthropometric measurements and body composition

Weight and height will be measured using a stadiometer. Body mass index (BMI) will be calculated as weight (kilograms)/height (meters squared). Individuals will be classified as overweight if their BMI is more than 25 kg/m^2^ but less than 30 kg/m^2^, and obese if their BMI is 30 kg/m^2^ or more. Body composition will be determined using a bioelectrical impedance analyzer (TANITA, model BC 420 MA) at the beginning and the end of each intervention phase.

#### Blood samples

Blood samples will be collected at each clinical evaluation. Blood samples will be centrifuged at 3000 rpm for 15 min to yield serum, aliquoted, and then stored at − 80 °C for subsequent analysis.

#### Urine and stool samples

Urine and fecal samples (four or five scoops totaling 4 g) will be collected in sterile containers with no solution before and after each intervention phase - with a total of six samples from each participant - and immediately frozen at − 20 °C, before being transferred to − 80 °C for subsequent analysis. The participants will be provided with urine and stool sample collection kits including containers and instructions. Participants will be invited to place the stool samples in the supplied sterile container with no solution, placed in a plastic bag and put into a household refrigerator immediately. Urine and stool samples will have to be delivered to the laboratory within 24 h in a styrofoam box containing ice packs.

#### Storage of biological specimens

The storage of biological specimens will be performed under appropriate conditions according to standard methods. Blood samples will be aliquoted and stored at − 80 °C for 4 years before being used or destroyed. Stored samples will be used exclusively for research purposes upon the consent of the donor. Sample destruction will be appropriately documented.

### Data management

Data will be collected in an electronic database. Identifiable data or other documents will not be recorded in the database and participants will be identified by a unique trial ID only. Hard copies of data sheets linking the participant identification number to the person’s contact details will be kept securely in a locked filing cabinet in a locked office, accessible only to key research team members. Participant files and other source data (including copies of protocols, questionnaires, original reports of test results, correspondence, records of informed consent, and other documents pertaining to the conduct of the study) will be kept for the maximum period permitted by the institution. All study data will be stored in the DASH-IN infrastructure, which is developed by ENPADASI. Thereby we will adhere to the findable, accessible, interoperable, and reusable (FAIR) principles. The data will be made open access upon publication. Within Europe, the ELIXIR infrastructure is coordinating data stewardship and management activities in the life sciences.

Multiple strategies will be employed to improve data quality during data collection, including accurate recruitment, a structured and time-limited protocol, the inclusion of a run-in period, the limitation of the burden and inconvenience of data collection to the participants, the development of a trusting and collaborative relationship between research units and participants, and double data-entry.

### Statistical analysis

The results will be expressed as mean plus/minus SD, median and range, or geometric mean with 95% confidence intervals (CIs) as appropriate. Categorical variables will be presented as frequencies and percentages. All data will be treated as paired samples from a cross-over study. The three interventions will be analyzed combining the results obtained in the three phases of the three groups. Outcomes will be analyzed within each group using the paired comparison Student’s *t* test to test whether the changes are statistically significant. The absolute change (mean baseline value subtracted from mean value after each intervention) will be estimated using the independent samples *t* test.

Raw sequences will be processed in the GM analysis, using a pipeline that combines PANDAseq [25] and QIIME [26]. The UCLUST software [27] will be used to bin high-quality reads into operational taxonomic units (OTUs) at 0.97 similarity threshold through an open-reference strategy. Taxonomy will be assigned through the Ribosomal Database Project (RDP) classifier, using the Greengenes database as a reference. Alpha diversity and rarefaction curves will be computed using different metrics, including the Faith’s phylogenetic diversity, the number of observed OTUs and the Shannon index. Beta diversity will be estimated by weighted and unweighted UniFrac distances, which will be used as input for principal coordinates analysis (PCoA). All statistical analysis will be performed using R and the packages vegan, stats, and made4. The significance of data separation in the PCoA will be tested using a permutation test with pseudo-F ratios (function Adonis in vegan). The Wilcoxon test for paired data will be used to assess significant differences in alpha diversity and taxon relative abundance between groups, and the Kruskal–Wallis test will be used for multiple comparisons. The *p* values will be corrected for false discovery rate (FDR) using the Benjamini-Hochberg method.

Permutational analysis of variance (PERMANOVA) adjusted for the order of treatment will be applied with two objectives: to assess the effect of the dietary interventions on PCoA scores of beta diversity metrics and to assess the effect of the dietary interventions and several metadata (SCFA levels, nutrient intake, clinical and biochemical parameters) on the whole microbial composition. Finally, the analysis will be performed at each taxonomic level (genus, family, order, class and phylum), in a separate model for each piece of metadata. Each analysis will be performed using a model including both the main effects and the interaction of the three dietary interventions. Because these tests assume normal data distribution, non-distributed data will be transformed into logs, and further analyses will be performed with the processed data. However, to facilitate interpretation, the log data will be again converted to the original scale (antilog) and presented as geometric means with 95% CIs. Spearman correlation coefficients between the changes in microbial composition, SCFA levels, nutrient intake, and in clinical and biochemical parameters will be computed and statistically tested for each dietary intervention.

Before starting the data analysis, the level, pattern and likely causes of the missingness in the baseline variables and outcomes will be investigated by preparing appropriate tables. This information will be used to determine whether the level and type of missing data has the potential to introduce bias into the analysis results or substantially reduce the precision of estimates for the proposed statistical methods. Sensitivity analyses will be undertaken, based on the assumption that missing outcomes are the worst possible, or the best possible, in different randomization groups. If these show that conclusions may differ based on missing values, then supplementary multiple imputations for missing values will be undertaken. These analyses will account for results of any losses to follow up insofar as they pertain to differences in measured variables (i.e. under the assumption of missing at random). Finally, subgroup analyses will be performed to analyze possible differences in the changes according to some characteristics of the study population, such as age, sex, categories of BMI, and physical activity. A *p* value <0.05 will be considered statistically significant. Statistical analyses will be performed using SPSS software for Macintosh (SPSS Inc., Chicago, IL, USA).

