## Abstract

**Background:**

Behçet’s syndrome (BS) is a systemic inflammatory disorder of unknown etiology, and it is characterized by a wide range of potential clinical manifestations. Recent evidence suggests that the gut microbiota (GM) in BS has low biodiversity with a significant depletion in butyrate producers. The aim of the present project is to investigate whether a dietary intervention could ameliorate the clinical manifestations and modulate the GM of individuals with BS.

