## Methods: participants, interventions, and outcomes

### Study design

The randomized, open, cross-over clinical trial will be conducted at the Careggi University Hospital, Florence, Italy. A cross-over design will be implemented to allow comparison of a lacto-ovo-vegetarian diet (VD), a Mediterranean diet supplemented with butyrate (MD-Bt), and a Mediterranean diet without any supplement (MD), as control, within the same individual. Participants will act as their own controls in cross-over studies, so individual differences will be controlled for, making the error variance smaller and subsequently reducing the sample size required to find a significant effect due to increased statistical power. The study design follows the Standard protocol items: recommendation for interventional trials (SPIRIT) guidelines (see Fig. 1 and supplementary file #1).

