## Discussion

BS is a systemic inflammatory disorder characterized by a wide range of potential clinical manifestations affecting different organs and tissues [1], with higher risk of mortality due to vascular-thrombotic and neurological affections [2]. The etiology remains unknown, and although various mechanisms have been proposed, it is not yet clear whether the microbiome has a role in this process [28]. To date, no studies are available that evaluate the effects of a nutritional intervention on BS. Thus, the aim of the project will be to understand the effect of a VD, MD-Bt, or MD on the manifestations of BS and, possibly, the role of the intestinal microbiota as a mediator of dietary effects in individuals with BS.

In a recent study by our group [4] there was low biodiversity in the composition of the GM in individuals with BS, and specific changes in the profiles of SCFA production [4]. In particular, a significant depletion of butyrate producers - such as *Roseburia* and *Subdoligranulum -* and a consequent decrease in butyrate production was demonstrated. Butyrate is the preferred fuel for colonocytes and one of the most representative SCFAs. It induces T regulatory cell differentiation through several mechanisms, so butyrate impairment in individuals with BS could promote reduced T regulatory cell-mediated control, thus promoting a powerful immunopathological T cell response [8] as suggested by the higher percentage of T helper (Th1)/Th17 cells in the intestinal mucosa observed in BS [9]. The presence of an altered GM in BS has recently been confirmed by Ye et al. [29] by analyzing fecal and saliva samples collected from 32 individuals with BS and 74 healthy controls. Fecal samples from individuals with BS contained greater levels of *Bilophila spp*. and several opportunistic pathogens (i.e. *Parabacteroides spp*. and *Paraprevotella spp*.) together with lower levels of butyrate-producing bacteria *Clostridium spp.* and methanogens (*Methanoculleus spp*. and *Methanomethylophilus spp*.). These differences have been associated with altered biological microbial functions with an enhanced oxidation–reduction process, a capsular polysaccharide transport system, and type III and IV secretion systems [29].

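### Before-after t tests within each diet are given a significance role, and nothing ties efficacy to the randomised contrast with the Mediterranean diet control

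*Protocol article*

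**What the plan says.** All references are to the protocol article.

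- **Metric.** Primary outcomes: "The metric used will be changes in means from the beginning to the end of each dietary intervention".
- **Pooling.** Statistical analysis: "The three interventions will be analyzed combining the results obtained in the three phases of the three groups". I therefore take the groups in the next sentence of that section to be the diets.
- **First test.** "Outcomes will be analyzed within each group using the paired comparison Student’s *t* test to test whether the changes are statistically significant". The threshold, p below 0.05, is given at the end of the same section.
- **Second test.** "The absolute change (mean baseline value subtracted from mean value after each intervention) will be estimated using the independent samples" *t* test. No pair of diets is named. Earlier in the paragraph the section says that the data are handled as paired cross-over data.
- **Control.** Study design: "a Mediterranean diet without any supplement (MD), as control, within the same individual".
- **Sample size.** 80 participants for 80% power at alpha 0.05 to detect a 50-point SSS difference between VD and MD; 90 are to be recruited.
- **Aims.** The Abstract wants to "investigate whether a dietary intervention could ameliorate the clinical manifestations and modulate the GM of individuals with BS". The Introduction asks whether VD or MD with butyrate (MD-Bt) could be beneficial. The Discussion wants to "understand the effect of a VD, MD-Bt, or MD on the manifestations of BS". None of the three adds a comparison with MD.
- **Setting.** Participants and dietitians are not blinded (Blinding). Dietitian counselling and phone calls accompany each diet (Interventions and participant timeline; Compliance).

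**The concern.** A before-after change within a diet contains the effect of the diet plus everything else that moves over three months. Here that includes the expectations of participants who know their diet and rate their own symptoms, the attention of a dietitian, and the natural course of the disease. Counselling and calls belong to all three diets, so an attention effect can recur in each of them. The paired test asks only whether the total change is zero.

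The randomised comparison is between diets, and whatever is common to the diets cancels there. The aims, however, are worded in absolute terms, and the only test of clinical outcomes whose stated purpose is significance is the within-diet one. Two errors are left open:

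1. One or more diets could be said to ameliorate the disease when none does.
2. VD could be called effective and MD not, because one p value falls below 0.05 and the other does not. That is not a test of VD against MD.

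**Working it through.** **Step 1: the plan's own figure.** N = 80 cannot be reproduced, because the article gives no SD and refers to a cited trial. It can only be solved backwards. With two-sided alpha 0.05 (an assumption, since sidedness is not stated) and 80% power, the sum of the normal quantiles is 2.8016.

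- Paired, n = 80: SD of the difference = 50 × √80 / 2.8016 = 159.6. If changes under two diets have equal SD and correlation ρ, the SD of one change is 159.6 / √(2(1 − ρ)). This is 112.9 at ρ = 0 and 159.6 at ρ = 0.5.
- Two parallel groups of 40: SD = 50 / (2.8016 × √(2/40)) = 79.8. This is not the trial's design and serves only as a low bound.

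The SD of change is therefore taken as 80 to 160, with 113 as the middle value.

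**Step 2: the within-diet test when no diet differs from another.** Let all diets share a non-diet improvement δ. The paired t statistic has 79 degrees of freedom and noncentrality δ / (SD/√80). The values of δ are assumptions; the article gives none.

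| SD of change | Noncentrality at δ = 25 | Significant, δ = 10 | Significant, δ = 25 | Significant, δ = 50 |
|---|---|---|---|---|
| 80 | 25/8.94 = 2.80 | 20% | 79% | about 100% |
| 113 | 25/12.63 = 1.98 | 12% | 50% | 97% |
| 160 | 25/17.89 = 1.40 | 9% | 28% | 79% |

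**Step 3: three diets together** (simulation, 10,000 runs, n = 80, SD 113, δ = 25). At least one of the three within-diet tests is significant in 87% of trials at ρ = 0, 81% at ρ = 0.3 and 74% at ρ = 0.5. All three are significant in 12%, 20% and 25%.

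**Step 4: one significant, the other not.** At ρ = 0, SD 113 and δ = 25, the chance that VD is significant and MD is not is 0.498 × (1 − 0.498) = 0.25, although the two diets are identical.

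**Step 5: the between-diet test in the same simulations.** The shared δ cancels in VD minus MD, so the result depends on neither δ nor the SD.

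- Paired comparison of the two changes: 4.7% to 5.2% false positives.
- Independent-samples test: 4.6% to 5.0% at ρ = 0, about 2% at ρ = 0.3 and about 0.5% at ρ = 0.5. It ignores the correlation, so it does not create false positives when ρ is positive. It does discard the precision that the cross-over was chosen to gain.

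**The case against.** The strongest reply is that the article never says efficacy is to be read from the before-after tests. The sentence after the quoted one applies an independent-samples test to the change. Such a test needs two sets of changes, so it is most naturally a comparison of diets. Study design names MD as control, and the sample size is set on VD versus MD. An active control is a legitimate design, and a journal article may leave the ranking of its tests to an analysis plan.

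Much of this stands. A reader might infer that the within-diet test is the decisive one, or that non-diet improvement will be reported as a diet effect. The text supports only that it could be. A reader might also infer that the trial has no valid comparison. It has one: MD is a randomised active control, and only the absolute effect of a diet is out of reach.

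Regression to the mean is tempting as a main argument but is weak here. Eligibility criteria set no symptom threshold, recruitment is also by advertisement, and the second and third baselines are scheduled visits rather than points chosen for high symptoms.

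What does not stand is the defence that this is only missing detail. The article names the within-diet test and states that its purpose is significance. The sentence that might supply the contrast names no diets, speaks of estimating the change, and uses a method that contradicts the paired handling declared just before it.

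**Conclusion.** The point holds in this form. The plan gives within-diet before-after tests inferential status and does not say that efficacy rests on the between-diet contrast. Its apparent between-diet test is unspecified as to diets and inconsistent with the paired design.

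As an illustration of size, with n = 80, no diet difference, an SD of change of 80 to 160 and a shared 25-point improvement, each within-diet test is significant in about 28% to 79% of trials. The between-diet test stays at or below about 5%. The SDs are back-solved from a sample size that gives none, and the shift has no source in the article. The percentages show how the test behaves and should not be read as a forecast of this trial's error rate.

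The between-diet contrast removes only what the diets share. Expectations that differ between diets remain in it, because participants know their diet.

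**What to change.** 1. In Statistical analysis, report the start-to-end change within each diet descriptively, as a mean with 95% CI, with no significance test and no efficacy claim.
2. State that efficacy conclusions rest on the within-person differences in change, VD minus MD and MD-Bt minus MD. Analyse them as paired cross-over data in place of the independent-samples test, for example in a mixed model with participant, period, sequence and diet.
3. Word the aims in the Abstract, the Introduction and the Discussion as comparisons with MD.

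This changes wording and analysis only, with no new visits or data. The cost is that the trial gives up any absolute claim of benefit for a single diet, including MD, which the design could not support in any case.
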